### **4.3 Withdrawal of individual subjects**

Subjects can leave the study at any time for any reason if they wish to do so without any consequences. The investigator can decide to withdraw a subject from the study for urgent medical reasons.

### **4.4 Replacement of individual subjects after withdrawal**

Dropout has been factored in at the sample size calculation. As we start treatment at group-level, individual subjects will not be replaced after withdrawal.

### **4.5 Follow-up of subjects withdrawn from treatment**

When a subjects withdraws from the study, reasons for drop-out will be examined. The participant will be asked to participate in follow-up assessments without taking part in the treatment part of the study. Adequate clinical care will be delivered as needed.

### **4.6 Premature termination of the study**

n case of detrimental effects as observed on group-level by RA's, clinicians or caregivers, the study will be terminated and adequate care will be provided.

## 5. SAFETY REPORTING

### 5.1 Section 10 WMO event

In accordance to section 10, subsection 1, of the WMO, the investigator will inform the subjects and the reviewing accredited METC if anything occurs, on the basis of which it appears that the disadvantages of participation may be significantly greater than was foreseen in the research proposal. The study will be suspended pending further review by the accredited METC, except insofar as suspension would jeopardise the subjects' health. The investigator will take care that all subjects are kept informed.

### 5.2 AEs, SAEs and SUSARs

#### 5.2.1 Adverse events (AEs)

Adverse events are defined as any undesirable experience occurring to a subject during the study, whether or not considered related to [the investigational product / the experimental intervention]. All adverse events reported spontaneously by the subject or observed by the investigator or his staff will be recorded.

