## 1. OBJECTIVES

### Primary Objective:

The primary aim of this project is to examine a shortened (+/- 20 sessions) and partly group-based version of the new and promising CBT approach tested in a chronic population (from now: 'Cognitive Behavioural Therapy – Social Activation' (CBTsa)), for its applicability and effectiveness in a recent-onset population. The CBTsa will be adjusted to the specific needs of the young recent-onset cohort.

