### 3. TREATMENT OF SUBJECTS

#### 3.1 Investigational product/treatment

##### Intervention

The CBTsa therapy is based on accumulating evidence that dysfunctional beliefs in conjunction with neurocognitive impairments can impede functioning [3]. The core assumption of this therapy is that modifying dysfunctional beliefs will lead to increased engagement in constructive social activity in individuals with prominent negative symptoms [7]. Its primary focus is to help participants overcome isolation and inactivity, and thereby improve quality of life [2], rather than focusing primarily on reduction of psychotic symptoms. CBTsa will target several defeatist beliefs and defeatist performance attitudes (e.g. 'if you cannot do something well, there is little point in doing it at all'). Apart from defeatist beliefs focusing on personal skills (such as cognitive functioning), negative expectancies regarding one's ability to experience pleasure (low anticipatory pleasure: 'I will not be able to enjoy this') are often reported by patients with schizophrenia. These types of beliefs combined with asocial beliefs (e.g. 'having close friends is not as important as most people say') have been found to result in (social) withdrawal and inactivity.

In the current intervention, Cognitive behavioural techniques will focus primarily on correcting these dysfunctional beliefs about pleasure, cognitive abilities, performance and social functioning. The intervention will consist of a group-based and an individual part, combining advantages of group processes and peer interaction with individual CBT. One major component of the group-based part is peer support (sharing experiences & practicing skills together with peers). The individual CBT sessions will be composed of personal case formulations, investigation of specific dysfunctional beliefs and behavioural experiments will be addressed.

In short, the intervention will constitute of:

1. Group sessions for 4 weeks, two sessions per week, 60 minutes per session, two trainers (a CBT therapist and a CBT assistant); eight participants, and;
2. Individual sessions (crystallizing learned skills, focus on individual needs) during 6-8 weeks, one session per week, 45 minutes per session.

The Group sessions (8 in total) will consist of:

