Psycho-education, peer support, buddy-forming, social goal setting, breaking goals down into steps and planning them, find obstacles and dysfunctional cognitions, behavioural experiments, and imagery for executing goal steps.

The Individual Sessions will contain: Individual case formulations (including the person's main dysfunctional beliefs and associated behaviours), continuation of working on social goals and countering obstacles to these goals. Also, psycho-education about symptoms, the role of cognition / beliefs and consequences of current behaviour will be addressed. Specific cognitive techniques that will be used to investigate dysfunctional beliefs and behaviour are a.o. 'Socratic dialogue', behavioural and cognitive experiments; dimensional evaluation of negative or stereotype self image etc); cognitive imagery techniques (imagining the steps needed to achieve new goals); behavioural techniques (activity scheduling, exposure to new situations that trigger anxiety etc.). Finally family members / important others will be involved. The choice for a particular combination of the above mentioned techniques will be based on the individual needs and goals of the patients.

To ensure treatment engagement and adherence, sessions will be adapted to the particular group under study: young patients recovering from recent episode psychosis. Adaptations for specific subgroups of patients may include specific illness characteristics (for example cognitive problems; concentration), gender and ethnic background. For example, sessions will be kept as low-level as possible and adapted to specific interests of the adolescent group: attention will be paid to sharing experiences, guaranteeing an open and safe treatment atmosphere; 'fun' parts (such as social games) will be included in the program. Further, treatment session time and duration will be adapted to the needs of individual patients (for example shorter en more frequent sessions). We will strive to address diversity (regarding age, gender, ethnic background etc) in the group- based part of the intervention as well as the individual part, for example by involving family members or important others to discuss implementation of treatment gains in patient's daily life.

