### **Study procedures**

After the participants have read and signed informed consent, and before treatment allocation, all patients will undergo a two hour during test battery carried out by an academic research assistant. Afterwards, participants will be asked to carry along an electronic device/ with an application with which participants are prompted by a beep at random intervals throughout the day (for a 6-day period) to report about their current experiences and withdrawal behaviour (see Experience Sampling Method (ESM; 9) table 1). The test battery will be repeated at the end of treatment, and 6-months post- treatment.

Patients allocated to the CBTsa condition will receive group sessions for 4 weeks, and 6-8 weeks weekly individual CBT sessions (see above).

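### Adverse events are recorded only when volunteered or noticed, while CBTsa patients have 14 to 16 more scheduled trial contacts than ST patients, so any by-arm count is open to detection bias

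*Protocol*

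**What the plan says.** Protocol section 5.2.1 defines the events broadly: "Adverse events are defined as any undesirable experience occurring to a subject during the study", whether or not related to the intervention. Its collection rule, the only one in the document, is "All adverse events reported spontaneously by the subject or observed by the investigator or his staff will be recorded". It does not say who counts as staff.

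The contact schedule differs by arm. Under Intervention in section 3.1, CBTsa patients receive "Group sessions for 4 weeks, two sessions per week, 60 minutes per session", confirmed by "The Group sessions (8 in total) will consist of", and then individual sessions "during 6-8 weeks, one session per week, 45 minutes per session". Controls receive standard treatment (ST) alone, which the CBTsa arm also receives. Both arms share the assessments: a baseline battery, and then "The test battery will be repeated at the end of treatment, and 6-months post- treatment". Table 1, which lists that battery, has no adverse-event question or checklist.

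**The concern.** Under a passive rule, an event is recorded only if there is an occasion to mention or notice it. The protocol gives one arm many more such occasions, in sessions that invite patients to talk about their difficulties. The assessments common to both arms do little to offset this, because none of them asks about adverse events. Section 4.2 also has assessors remind patients not to discuss allocation, which may discourage remarks about therapy.

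What is at stake is how any by-arm listing of adverse events can be read. An excess in CBTsa could come from closer observation alone, and similar counts could conceal missed events in ST. An analysis plan cannot repair this later, because events that nobody asked about are not in the data.

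**Working it through.** **Step 1: count the scheduled contacts.** Inputs are from section 3.1 and Study procedures.

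- Group sessions: 4 weeks × 2 per week = 8, which reproduces the protocol's own total.
- Individual sessions: 6 to 8 weeks × 1 per week = 6 to 8.
- Extra CBTsa contacts: 8 + 6 = 14 to 8 + 8 = 16, spread over 4 + 6 = 10 to 4 + 8 = 12 weeks.
- All trial contacts, with 3 assessments per arm: 17 to 19 against 3, a ratio of 5.7 to 6.3.
- After baseline, with 2 assessments per arm: 16 to 18 against 2, a ratio of 8 to 9.

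The session count is nominal. The Primary Objective describes "a shortened (+/- 20 sessions) and partly group-based version", which 14 to 16 does not reproduce; the two statements need reconciling. Section 3.1 also lets sessions be adapted, "for example shorter en more frequent sessions". About 20 sessions, or more frequent ones, would widen the imbalance.

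**Step 2: illustrate the effect on recorded events.** Assume the same true burden in both arms and a constant, independent chance p that a contact puts an event on record. For k contacts,

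P(at least one recorded event) = 1 − (1 − p)^k.

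The protocol gives neither p nor the number of routine-care contacts that would feed the record. Both are assumptions, and routine contacts are taken as equal in the two arms. With p = 0.05:

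| Routine contacts counted per patient | k, CBTsa | k, ST | CBTsa | ST | Ratio at lower k |
|---|---|---|---|---|---|
| 0 | 17 to 19 | 3 | 58.2% to 62.3% | 14.3% | 4.08 |
| 12 | 29 to 31 | 15 | 77.4% to 79.6% | 53.7% | 1.44 |
| 36 | 53 to 55 | 39 | 93.4% to 94.0% | 86.5% | 1.08 |

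For example, 1 − 0.95^17 = 0.582 and 1 − 0.95^3 = 0.143. With p = 0.02 and trial contacts only, the figures are 29.1% to 31.9% against 5.9%.

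**Step 3: sensitivity to the form of the model.** Alternatively, let each event be caught with probability 1 − (1 − q)^k over post-baseline contacts, with q between 0.02 and 0.20. The CBTsa to ST ratio of recorded rates is then 2.7 to 7.7 with trial contacts only, 1.04 to 1.84 with 12 routine contacts, and 1.00 to 1.24 with 36. The direction is stable. The size depends mainly on whether routine care feeds the record.

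**Step 4: after the fix.** If by-arm summaries use only a question set given at the two shared post-baseline visits, scheduled opportunities are 2 against 2.

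**The case against.** The strongest reply is that the protocol plans no comparison of harms. Adverse events are not among the main, secondary or other parameters, safety is not an objective, and the statistical section contains no adverse-event analysis. That stands. The point concerns any tabulation by arm, not a planned test.

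Second, ST patients are not unobserved between assessments. Section 2.1 places every participant in intensive outreach care, as inpatients, day patients or outpatients. If those clinicians report events, the gap shrinks sharply, as the table shows. This also stands as a limit on size, but the protocol neither requires them to report nor says whether they are staff.

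Third, PANSS, CDSS, GAF, CAN and TiC-P capture symptoms, functioning, needs and health-care use in the same way in both arms. That is true and useful, but none of them is an adverse-event record and nothing links them to section 5.2.1.

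A reader might infer more than the text supports:

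- **That the termination rule rests on biased counts.** Section 4.6 acts on detrimental effects seen at group level by research assistants, clinicians or caregivers, not on adverse-event counts by arm.
- **That the annual report does.** Section 6.8 asks for serious events, with no comparison by arm.
- **That the no-risk statement depends on these data.** Section 6.3 bases it on the CBT literature.
- **That the 6 months after treatment add to the imbalance.** That interval has no scheduled trial contact in either arm, so it cannot cause unequal detection.

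**Conclusion.** The concern holds in a limited form. The collection rule is purely passive, the battery has no solicited question, and CBTsa adds 14 to 16 scheduled trial contacts during treatment. Any by-arm count is therefore exposed to detection bias, most likely towards more recorded events in CBTsa.

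Its size cannot be fixed from the protocol. At an assumed 5% capture per contact, the gap at the lower session count runs from about 44 percentage points (58.2% against 14.3%) with trial contacts only to about 7 points (93.4% against 86.5%) with 36 routine contacts per patient also counted. The first figure is the extreme case. It would be tempting to conclude that by-arm counts are uninterpretable, or that CBTsa will show several times as many events. Neither follows, because both require that routine clinicians contribute nothing, which the protocol leaves open.

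The change is worth making because it is cheap and has to be made at data collection.

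**What to change.** Amend section 5.2.1 as follows.

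1. At the end-of-treatment and 6-month visits, every participant in both arms completes the same short adverse-event question set covering the interval since the last assessment.
2. It is given after the PANSS and BNSS ratings, as a self-completed form that the blinded assessor does not see, or is read by existing unblinded staff. Asking after the ratings is not enough: an open answer at end of treatment can reveal allocation to an assessor who rates the same patient again at 6 months.
3. Any by-arm summary uses these solicited reports. Events noted in therapy sessions or routine care are still recorded, but listed separately.
4. State whether CBTsa therapists and ST clinicians count as staff for this rule.

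The cost is a few extra minutes at two existing visits, more recorded non-serious events, and a small risk of unblinding that the self-completed form limits. If the blind is broken, section 4.2 already has another research worker do the later assessments.

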## STATISTICAL ANALYSIS

### 5.3 Primary study parameter(s)

Our primary and secondary study parameters are all of quantitative and continuous nature. Evaluation of randomisation procedure and differential drop-out will be analysed by means of independent samples T-tests. We will apply mixed model repeated measures analyses to examine the effects of the intervention on negative symptoms over time, and the differential effect of the CBTsa condition relative to ST. In addition, we will make use of LISREL models to correct for attenuation due to measurement error.

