### **2.4 Sample size calculation**

The effectsize to calculate our estimated sample size is based upon a recent groundbreaking study of Grant and colleagues (one of our co-applicants), who carried out an intervention with

similar ingredients as ours in a more chronic schizophrenia population. In their study, also specifically targeted to reduce negative symptoms and to socially activate their patient sample, they found that patients receiving cognitive therapy showed a greater mean reduction in avolition-apathy (adjusted mean [SE], 1.66 [0.31] vs 2.81 [0.34], respectively;  $P=.01$ ; between-group  $d=-0.66$ ) as compared with those receiving standard treatment. This outcome measure is comparable to the 'social withdrawal' outcome measure used in our study. Based on this results, and upon the commonly hold assumption that recent onset subjects are more likely to change than the more chronic population, we estimated to find an effectsize of (at least) .66 in our study as well. With an alpha of 0.5; power=80%; effect-size .66 [3], this would mean we need 36 participants per group to detect a true treatment difference. Taking into account an expected dropout rate of 20%, we would need to include  $72 + 20\% = 87$  participants = 44 per group.

To take into account the 'variance inflation' factor (due to our multi-center design), we calculated the Intra Class Correlation Coefficient of the PANSS negative symptom scores of a study targeting a similar population and setting (GROUP), in which 4 centers participated. The ICC in this study was .146. Following the literature, we then used the following formula:  
 $1 + (m-1) \times \text{ICC}$  (m= number of participating centers).

For our study this means we have to increase the sample size (87) by a factor of:

$$1 + (3-1) \times .146 = 1.292$$

This results in a total estimated sample size of:  $1.292 \times 87 = 112$  individuals (56 per condition)

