**5.5 Other study parameters**

Substance abuse, and socio-demographic variables (e.g. age, gender, medication prescription) will be added to the model as possible confounders.

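### The protocol does not say how the baseline negative-symptom score enters the primary mixed model; a plain arm-by-time contrast would be less precise than a baseline-adjusted one

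*Protocol*

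**What the plan says.** Section 5.3 fixes the type of primary analysis: "We will apply mixed model repeated measures analyses to examine the effects of the intervention on negative symptoms over time", together with the differential effect of CBTsa relative to standard treatment. Section 5.4 applies equivalent analyses to the secondary scales.

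The Study Design and Study procedures sections place the same test battery at baseline, directly after treatment and 6 months later. The Summary names the main endpoint as a change in negative symptoms.

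On covariates, section 5.5 says: "Substance abuse, and socio-demographic variables (e.g. age, gender, medication prescription) will be added to the model as possible confounders". The baseline value of the outcome is not named there or anywhere else as a model term. No section says that the arm means are to be held equal at baseline.

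On timing, the Study procedures section says that "before treatment allocation, all patients will undergo a two hour during test battery carried out by an academic research assistant". Section 6.2 instead places the baseline assessments soon after randomisation.

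**The concern.** The baseline score of the outcome is usually among the best predictors of its later values, and here it is collected in everyone. The protocol names weaker predictors for the model and leaves this one unmentioned.

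Taken at face value, a repeated-measures model over time with an arm-by-time test compares change from baseline between the arms. That is a valid comparison, but it carries the full noise of the baseline measurement. Conditioning on baseline, or constraining the arms to a common baseline mean, uses the same data more efficiently.

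Two things are at stake:

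- **Power.** Section 2.4 sizes the trial for 80% power at an effect of 0.66 with 36 per group. On the change contrast, that power is reached only if rho is about 0.5 or more.
- **Chance imbalance.** If the arms happen to differ at baseline, a change contrast subtracts the whole difference, although only a fraction rho of it is expected to persist at follow-up. It therefore over-corrects.

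**Working it through.** **Inputs**

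- Effect 0.66 (section 2.4: "we estimated to find an effectsize of (at least) .66 in our study as well"), taken in units of the post-treatment score SD. This unit is an assumption.
- Power 80% and 36 per group (section 2.4: "we need 36 participants per group to detect a true treatment difference").
- Alpha is printed as 0.5. I use two-sided 0.05, because only that reproduces 36.
- Expected dropout 20%, total 112 (56 per arm) and variance inflation factor 1.292, all from section 2.4.
- rho is not given in the protocol. I assume 0.3 to 0.7, with equal variances and equal correlations across visits.

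**Reproducing the plan's own figure**

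n per arm = 2(1.960 + 0.842)² / 0.66² = 36.04, which matches the stated 36. Alpha 0.5 would give 11 per arm, and one-sided 0.05 would give 29. The exact t-test power at 36 per arm is 78.9%. The later steps also follow: 72 × 1.20 = 86.4, taken as 87, and 87 × 1.292 = 112.4, taken as 112.

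**Variance of the treatment contrast at one follow-up visit, in units of 2σ²/n**

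- Baseline as a response with a free arm difference (arm-by-time contrast): 2(1-rho).
- Baseline as a covariate, or as a response with arm means constrained equal: 1-rho².
- Ratio, adjusted to change: (1-rho)(1+rho) / [2(1-rho)] = (1+rho)/2, never above 1.

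A generalised least squares calculation with three occasions gave the same factors for the free and the constrained models.

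**Power**

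The effective effect size is 0.66/√[2(1-rho)] for the change contrast and 0.66/√(1-rho²) for the adjusted contrast. At rho = 0.4 these are 0.66/√1.2 = 0.602 and 0.66/√0.84 = 0.720. Two-sample t-test, two-sided 0.05:

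| Assumed rho | Variance ratio | Change, 36 per arm | Adjusted, 36 per arm | Gain, 36 per arm (points) | Gain, 45 per arm (points) |
|---|---|---|---|---|---|
| 0.3 | 0.65 | 65% | 83% | 18 | 16 |
| 0.4 | 0.70 | 71% | 85% | 14 | 12 |
| 0.5 | 0.75 | 79% | 89% | 10 | 8 |
| 0.6 | 0.80 | 87% | 93% | 6 | 4 |
| 0.7 | 0.85 | 95% | 97% | 3 | 1 |

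The 45 per arm is 56 × 0.80 = 44.8 completers and ignores clustering. Dividing by the protocol's own factor gives 45/1.292 = 34.8 effective patients per arm, so on its own reasoning the 36-per-arm columns are the closer guide.

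**Chance imbalance**

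Let δ be an observed baseline difference between arms. Its expected carry-over to follow-up is rho·δ. A change contrast subtracts δ, which leaves an error of -(1-rho)δ; at rho = 0.5 that is half of δ in the opposite direction. Adjustment removes rho·δ.

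**The case against.** The strongest reply is that the protocol is silent rather than wrong. Whether baseline is a covariate, a free response or a constrained response is often settled in a SAP, which is not at hand. Section 5.5 may be a list of possible confounders and no more, so the absence of the baseline score there is weak evidence. If the model in mind already constrains the arm means at baseline, nothing is lost. These points stand in part, and they are why the gain is conditional. But the protocol itself chooses the model and names covariates, so adding the baseline form is a specific improvement to text that already exists.

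A reader might infer that baseline is left out of the primary model altogether, and that chance imbalance goes uncorrected. The documents do not support this. The wording about effects over time, the three assessments and the change endpoint all point to baseline as the first repeated response. In that case a baseline difference is subtracted, only too fully. A loss measured against a model of follow-up scores alone therefore does not describe this plan.

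A reader might also infer that the trial is underpowered. That does not follow either. On the change contrast at 36 per arm, power falls clearly below the planned 80% only when rho is under 0.5. At 45 per arm, ignoring clustering, it is 87% at rho 0.5.

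Finally, section 2.4 reports the 0.66 beside adjusted means from the cited trial. If it is already in baseline-adjusted SD units, the absolute powers above are too high. The variance ratio (1+rho)/2 is unaffected.

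**Conclusion.** The point holds as one of precision and pre-specification. Neither form is biased under randomisation.

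Read most naturally, the primary contrast has variance proportional to 2(1-rho), where the same data allow 1-rho². On assumed rho of 0.3 to 0.7 the forgone power is about 18 down to 3 points at 36 per arm, and about 16 down to 1 at 45 per arm without clustering. It is zero if the arm means are already constrained equal at baseline, which the protocol does not state.

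These sizes rest on the assumed rho, equal variances and correlations across visits, two-sided alpha 0.05, and an effect of 0.66 in post-score SD units.

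The benefit also relies on a baseline taken before allocation, and the Study procedures section and section 6.2 disagree on that.

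**What to change.** - **Section 5.3:** model the end-of-treatment and 6-month scores with arm, visit, arm-by-visit, the baseline score of the same scale and its interaction with visit. Alternatively, keep baseline as a response and constrain the arm means to be equal there.
- **Section 5.5:** add the baseline value of the outcome to the covariates.
- **Section 5.4:** use the same form for the secondary scales, each with its own baseline.
- **Study procedures and section 6.2:** reconcile the timing of the baseline assessment relative to randomisation. The equal-means constraint in particular depends on a pre-allocation baseline.
- Quote any power gain together with the rho it assumes.

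The cost is a few sentences of wording and one or two degrees of freedom. No patients, visits or measurements are added. The choice should be fixed before unblinding, so that it is not made among analyses that could give different answers.
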